### 6.3.2 Study drug dosing schedule:

| **Treatment Groups** | **Medications** | **Day 0** | **Day 1** | **Day 2** |
| --- | --- | --- | --- | --- |
| CQ/SP | CQ | 10 mg/kg | 10 mg/kg | 5 mg/kg |
| SP | 25 mg/kg sulfa component | Placebo if 3-arm  study | Placebo if 3-arm  study |
| AQ/SP | AQ | 10 mg/kg | 10 mg/kg | 5 mg/kg |
| SP | 25 mg/kg sulfa component | Placebo if 3-arm  study | Placebo if 3-arm  study |
| AS/AQ | AS | 4 mg/kg | 4 mg/kg | 4 mg/kg |
| AQ | 10 mg/kg | 10 mg/kg | 5 mg/kg |

### FOLLOW-UP EVALUATION AND PROCEDURES

7.1. Follow-up schedule:

Patients will go home on Day 0 and will be asked to return to the clinic for follow-up on Days 1, 2, 3, 7, 14, 21, 28, and any unscheduled day that they feel ill. All patients will be reimbursed the cost of their transport to and from the clinic. Details about the location of the patient’s residence will be obtained and if a subject does not return for a scheduled clinic follow-up appointment, the study personnel shall visit them at home. Patients who return on Day 1 and fail to fulfil the criteria of *P. falciparum* mono-infection with a parasite density of > 2000 parasites/ul and < 200,000 parasites/ul will be excluded from further study and referred to OPD for management. At each repeat visit, temperature will be measured and a focused physical examination will be performed. A finger prick blood sample will be obtained on Days 2, 3, 7,14, 21 and 28 (and any extra day) to repeat thick blood smears and to save on filter paper. Haemoglobin will be re-evaluated either on day 28 or at the time of clinical treatment failure. All thick smears will be assessed for parasite density and presence of gametocytes. Any patient who is suspected of clinical treatment failure after Day 3 will have a repeat thick and thin smear obtained.

Follow-up Schedule

|  | **Day 0** | **Day 1** | **Day 2** | **Day 3** | **Day 7** | **Day 14** | **Day 21** | **Day 28** | **Extra Day** | **When necessary** |
| --- | --- | --- | --- | --- | --- | --- | --- | --- | --- | --- |
| Study medications | X | X | X |  |  |  |  |  |  |  |
| History | X | X | X | X | X | X | X | X | X |  |
| Temperature measurement | X | X | X | X | X | X | X | X | X |  |
| Physical exam | X | X | X | X | X | X | X | X | X |  |
| Neurologic exam (3-arm study only) | X |  |  |  | X | X | X | X | * |  |
| Thick blood smear | X |  | X | X | X | X | X | X | X |  |
| Thin blood smear | X |  |  |  |  |  |  |  |  | CTF after day 3 |
| Filter paper sample | X |  |  | X | X | X | X | X | * |  |
| Haemoglobin | X |  |  |  |  |  |  | X | * | If CTF, on day of failure |
| Assessment for adverse drug event | X | X | X | X | X | X | X | X | X |  |

X = perform this task

* As indicated

### 7.2. Assessment for adverse events related to study medications (Appendix 10):

### 7.2.1 Definitions of adverse events:

A description of expected adverse events for each of the study medications shall be obtained from package inserts of the study medications. The following definitions will be used according to NIAID guidelines:

- Adverse event: any untoward medical occurrence, including dosing errors, that may arise during administration of study agent, and which may or may not have a causal relationship with the study agent.
- Unexpected adverse event: any adverse experience that has not been previously observed (i.e. Included in the labeling), whether or not the event is anticipated because of the pharmacologic properties of the study agent
- Serious adverse event: any adverse experience that results in any of the following outcomes: death; life threatening experience; inpatient hospitalization; persistent or significant disability or incapacity; or specific medical or surgical intervention to prevent one of the other serious outcomes listed in the definition.

### 7.2.2. Identification of adverse events:

At each follow-up visit (days 1, 2, 3, 7, 14, 21, 28, and any unscheduled day), study clinicians will assess patients according to a standardized clinical record form (Appendix 14). All signs and symptoms present will be graded as mild, moderate, severe, or life threatening according to examination guidelines (Appendix 6). An AE will be defined as a sign or symptom of untoward medical occurrence arising or increasing in severity compared to the previous day’s record.

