**Appendix 5. Guidelines for Grading Patient Symptoms**

|  | **Grade 1**  **MILD** | **Grade 2**  **MODERATE** | **Grade 3**  **SEVERE** | **Grade 4**  **LIFE THREATENING** |
| --- | --- | --- | --- | --- |
| **Subjective fever in the past 24 h** | N/A | Present (Yes) | N/A | N/A |
| **Convulsion** | N/A | N/A | Localized or generalized seizure | Status epilepticus |
| **Headache*** | Mild, no therapy required | Transient, moderate; therapy required | Severe; responds to initial narcotic therapy | Intractable; requires repeated narcotic therapy |
| **Anorexia** | Decreased appetite, but still taking solid food | Decreased appetite, avoiding solid food | Refusing to breast feed, appetite very decreased, no solids or liquids taken (< 2 years < 12 hr; > 2 years < 24 hr) | Refusing to breast feed, appetite very decreased, no solids or liquids taken (< 2 years < 12 hr; > 2 years < 24 hr) |
| **Nausea*** | Mild discomfort; maintains reasonable intake | Moderate discomfort; intake decreased significantly; some activity limited | Severe discomfort; no significant intake; activities limited | Minimal fluid intake |
| **Vomiting** | Transient emesis | Occasional or moderate vomiting | Orthostatic hypotension or IV fluids required | Hypotensive shock or hospitalization required for IV fluid therapy |
| **Abdominal pain*** | Mild | Moderate – no treatment needed | Moderate to severe – treatment needed | Severe – hospitalized for treatment |
| **Diarrhea** | Transient 3-4 loose stools/day | 5-7 loose stools/day | Orthostatic hypotension or > 7 loose stools/day or IV fluids required | Hypotensive shock or hospitalization for IV fluid therapy required |
| **Cough** | Transient – no treatment required | Continuous, requires treatment | Uncontrolled | Cyanosis, stridor, severe shortness of breath |
| **Pruritis** | Pruritis without rash | Pruritic rash, pruritis without rash that disturbs sleep | Mild urticaria | Severe urticaria, anaphylaxis, angioedema |
| **Tinnitus*** | Mild ringing or roaring sound | Moderate ringing or roaring sound | Severe ringing or roaring sound with associated hearing loss | N/A |

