### APPENDIX 10. Adverse Event Reporting Guidelines

On Day 0 perform a careful history and physical exam and record your findings on the case record form (CRF), grading the patient reported symptoms and exam findings according to the guidelines presented in Appendices 3 and 4. Record the hemoglobin value and grade (Appendix 5) on the CRF as soon as they are available. All Day 0 values will serve as the patient’s baseline.

On all follow-up days, assess and grade the patient-reported symptoms and physical exam signs according to the guidelines in Appendices 3 and 4. Record the follow-up hemoglobin results obtained on Day 28 (and any extra day) and grade according to the guidelines in Appendix 5.

At each follow-up visit, evaluate the CFR for any reportable adverse events. Review for symptoms, physical exam signs, and hemoglobin results that are > grade 2 and are new or worsening by comparing the grade assigned on the follow-up day to the previous day’s record.

If a new or worsening symptom, sign, or laboratory value is present (increasing grade compared to the previous day’s value and > grade 2), answer “YES” in the appropriate column for reporting adverse events on the CRF (otherwise, answer “NO”).

An adverse event is defined as any “untoward” (unfavorable or undesirable) medical occurrence in a patient who has received a medication that may or may not be related to this treatment. Any event (patient-reported symptom, physical exam finding, or laboratory value) that occurs after treatment with a study medication that is new or worsening from Day 0 should be considered a possible adverse event, regardless of whether you think that the treatment caused the event.

The following scenarios are examples of adverse events (AEs):

|  | **Day 0** | **Day 1** | **Day 2** |
| --- | --- | --- | --- |
| Nausea | 0 | 0 | 2 |

AE = nausea on Day 2

|  | **Day 0** | **Day 1** | **Day 2** | **Day 3** |
| --- | --- | --- | --- | --- |
| Nausea | 2 | 1 | 0 | 2 |

AE = nausea on Day 3

For each new / worsening event of > grade 2, the following information will be collected on the Adverse Event Record Form:

1. Description of event
2. Date of event onset
3. Date event reported
4. Maximum severity of the event
5. Maximum suspected relationship of the event to study medication
6. Is the event serious?
7. Initials of the person reporting the event
8. Was the event episodic or intermittent in nature?
9. Outcome
10. Date event resolved

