****(Grade on scale of 0-4: normal = 0; mild abnormality = 1; moderate = 2; severe = 3, life-threatening = 4)***

***† Adverse event reported if hemoglobin measured after Day 0 is grade > 2. Notify Kampala core facility immediately of all serious adverse events.***

| RECORD OF ADDITIONAL MEDICATION GIVEN DURING STUDY | | | | | |
| --- | --- | --- | --- | --- | --- |
| **Medication (a)** | **Indication (b)** | **Dose (c)** | **Duration (d)** | **Date started (e)** | **Study day (f)** |
| **60.** |  |  |  |  |  |
| **61.** |  |  |  |  |  |
| **62.** |  |  |  |  |  |
| **63.** |  |  |  |  |  |
| **64.** |  |  |  |  |  |
| **65.** |  |  |  |  |  |
| *66.* |  |  |  |  |  |
| **67.** |  |  |  |  |  |
| **68.** |  |  |  |  |  |
| **69.** |  |  |  |  |  |
| **70.** |  |  |  |  |  |

| **UMSP clinical record form (4): Two-Arm Study (CQ/SP, AQ/SP** | | | |
| --- | --- | --- | --- |
| **Patient**  **Initials:** | **1. Study Number: U**|___|___|___|___|___| | **2. Day 0 Date:** |___|___|/|___|___|/|___|___|  ***day month year*** | **3. Treatment Number:** |___|___|___| |

| complete efficacy outcome | |
| --- | --- |
|  ETF     LCF   LPF   ACPR     N/A (Tick appropriate Incomplete Efficacy Outcome **)** | If failed, **STUDY DAY** of clinical failure (0-28) __________  **Reason for ClinicalFailure:**   Severe malaria/danger signs with parasitemia Days 0-3  Specify criteria _________   Severe AE requiring change in treatment Days 0-2  Specify criteria _____________   Day 2 parasite count > Day 0 count   Parasitemia on Day 3 with temperature > 37. 5   Day 3 parasite count > 25% Day 0 count   Severe malaria with parasitemia Days 4-28  Specify criteria __________________   Parasitemia on Days 4-28 with temperature > 37. 5 OR History of fever in past 24 hours. |

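### The adverse-event rule uses two reference points and the CRF haemoglobin footnote uses none, so an improving haemoglobin can be recorded as an AE

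*Protocol*

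**What the plan says.** Section 7.2.2 gives the general definition: "An AE will be defined as a sign or symptom of untoward medical occurrence arising or increasing in severity compared to the previous" day's record.

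Appendix 10 contains both reference points:
- **Previous record.** Its CRF-review instruction picks out symptoms, signs and "hemoglobin results that are > grade 2 and are new or worsening by comparing the grade assigned on the follow-up day" with the previous day's record. It repeats that comparison in the next instruction.
- **Day 0.** It also says "All Day 0 values will serve as the patient’s baseline", and that any event after treatment, laboratory values included, "that is new or worsening from Day 0 should be considered a possible adverse event".
- **Worked example.** For nausea graded 2, 1, 0, 2 on Days 0 to 3 it concludes "AE = nausea on Day 3".

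In Appendix 15, the symptom and examination footnotes (forms 1 and 2) require a new or worsening finding. The laboratory footnote (form 3), in both the two-arm and three-arm versions, does not: "Adverse event reported if hemoglobin measured after Day 0 is grade > 2".

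In Appendix 5, the Grade 3 and Grade 4 cells for anorexia carry the same text: "Refusing to breast feed, appetite very decreased, no solids or liquids taken (< 2 years < 12 hr; > 2 years < 24 hr").

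Section 4.2.2 makes the proportions of patients with any AE, with a serious AE, and with AEs by specific sign or symptom the safety and tolerability comparisons. Section 7.2.3 keeps mild AEs in the analysis.

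**The concern.** The proportion of patients with an AE depends on what each finding is compared with. Two comparisons are written down, and nothing says which one defines the endpoint. The haemoglobin footnote goes further: with no comparison at all, it turns a low but recovering value into an AE.

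This is foreseeable. Section 5.2 excludes only haemoglobin below 5.0 g/dL, so patients may enter at Grades 2 to 4, and section 6.2 gives iron to children below 10.0 g/dL. At stake is whether the arms' AE proportions describe treatment or partly describe baseline anaemia and the day on which haemoglobin was measured.

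**Working it through.** The protocol states no AE rate, AE power or AE sample size, so there is no figure of its own to reproduce. The check is to apply each written rule to the same records.

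**1. The two reference points.** Write g0 for the Day 0 grade and gi for the grade at visit i.
- Previous-record rule: AE if gi > g(i-1).
- Day 0 rule: AE if gi > g0.

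For nausea 2, 1, 0, 2, the Day 3 comparison with the previous record is 2 > 0, an AE. Against Day 0 it is 2 > 2, not an AE. Appendix 10's other example (0, 0, 2) is an AE under both.

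**2. How the rules relate.** All sequences of Day 0 plus four visits with grades 0 to 4 were listed: 5^5 = 3,125.

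| Minimum grade counted | AE, previous record | AE, Day 0 | Previous record only | Day 0 only |
|---|---|---|---|---|
| 1 | 2,999 | 2,146 | 853 | 0 |
| 2 | 2,906 | 2,131 | 775 | 0 |
| 3 | 2,582 | 2,001 | 581 | 0 |

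Every Day 0 AE is also a previous-record AE, so incidence under section 7.2.2 can only equal or exceed incidence under the Day 0 sentence. These are counts of possible patterns, not of patients, and give no estimate of the gap.

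**3. Haemoglobin.** Grades come from Appendix 6, Table C: Grade 1 is 9.5–10.5, Grade 2 is 8.0–9.4 (the upper limit is printed without its decimal point), Grade 3 is 6.5–7.9 and Grade 4 is below 6.5 g/dL.

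| Day 0 to follow-up (g/dL) | Grade | CRF footnote as printed (> 2) | CRF footnote read as at least 2 | Appendix 10 (worsening and at least Grade 2) |
|---|---|---|---|---|
| 5.5 to 7.5 | 4 to 3 | AE | AE | no |
| 7.0 to 9.0 | 3 to 2 | no | AE | no |
| 9.0 to 9.3 | 2 to 2 | no | AE | no |
| 11.0 to 9.0 | 0 to 2 | no | AE | AE |

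The first row is an improvement recorded as an AE on either reading. The at-least-2 reading is the likelier intention: section 7.2.3 requires a report form for moderate events, Appendix 10 scores maximum severity from 2 upwards, and the AEs in both its examples are Grade 2.

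**4. Direction between arms.** Section 7.1 takes follow-up haemoglobin on Day 28 or at clinical failure. Section 8.1 expects failure of 15% v 5% (ratio 15/5 = 3) or 10% v 2% (ratio 10/2 = 5). The share of patients measured early is therefore expected to differ by arm, and false-flag rates need not be equal.

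To show only that the sign is open, assume true AE risks of 20% and 10%. Let false flags fall at rate q on patients without a true AE, so that the observed risk is p + (1 − p)q:
- q = 20% v 10%: 0.20 + 0.80 × 0.20 = 0.36 and 0.10 + 0.90 × 0.10 = 0.19, a difference of 17 points.
- q = 10% v 20%: 0.20 + 0.80 × 0.10 = 0.28 and 0.10 + 0.90 × 0.20 = 0.28, a difference of 0.

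Against a true difference of 10 points, the error can run either way. None of these p and q values comes from the protocol.

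**5. Timing words.** After Day 3 the scheduled visits are Days 7, 14, 21 and 28, so a comparison with the previous day's record cannot be made literally.

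**The case against.** The previous-record rule clearly dominates: it is in section 7.2.2 and twice in Appendix 10, both worked examples fit it, and the Day 0 sentence speaks only of a possible AE. All sites receive the same forms. The haemoglobin footnote is a reporting trigger, and section 7.2.3 shows that reporting and analysis are separate. Sections 4.2.2 (third safety outcome) and 7.2.2 speak of signs and symptoms, and an analysis plan not shown here could settle whether haemoglobin flags count.

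Much of this stands. It does not remove the conflict over haemoglobin, because Appendix 10 lists laboratory values among AEs, and the any-AE outcome in section 4.2.2 is not limited to signs and symptoms.

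Nor is Day 0 plainly the better reference. Patients enter acutely ill, and requiring a grade above Day 0 would lose an event that returns after the malaria symptoms have cleared, which the nausea example is written to capture.

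Several stronger readings are tempting but unsupported:
- **Three baselines.** There are two reference points and one haemoglobin rule with none.
- **Any low haemoglobin is flagged.** Grade 1 never is, and read literally only values below 8.0 g/dL are.
- **Resolving malaria symptoms count as AEs.** Every symptom and sign rule needs a new or rising grade.
- **A Grade 4 anorexia entry is automatically serious.** Appendix 10 says seriousness is not directly tied to severity.

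**Conclusion.** The point holds as an internal contradiction with one rule that is wrong as printed. Two reference points compete for the AE definition, and the CRF haemoglobin footnote drops a condition that Appendix 10 requires. An improvement from 5.5 to 7.5 g/dL is recorded as an AE on any reading; one from 7.0 to 9.0 g/dL is recorded if the sign means at least Grade 2. The identical anorexia cells leave Grade 3 and Grade 4 counts for that symptom undefined.

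The effect on the AE comparison rests on haemoglobin flags entering the any-AE endpoint, which Appendix 10 implies but no section states. A reader might infer that AE incidence is inflated and arm differences diluted. The documents do not support that as a general claim: excess is shown only relative to the Day 0 rule, or to a worsening rule for haemoglobin, and dilution would need equal false-flag rates in the arms. Because haemoglobin timing follows failure, bias in either direction is possible. Its size cannot be derived from the documents.

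**What to change.** - Add the new-or-worsening condition to the haemoglobin footnote in both CRF versions. The only routine earlier haemoglobin is Day 0, so the comparison is unambiguous.
- State in the same footnotes and in Appendix 10 whether the threshold is Grade 2 and above or above Grade 2.
- Reconcile section 7.2.2 and Appendix 10 so that one named reference point defines the AE incidence endpoint, and say whether haemoglobin counts in it. Report the other reference point as a sensitivity analysis.
- Where the previous-record comparison is kept, refer to the previous visit instead of the previous day.
- Make the Grade 3 and Grade 4 anorexia cells in Appendix 5 distinguishable, with wording set by the clinical team.

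The cost is wording in one section, two appendices and one footnote in each of the two CRF versions. Symptom and sign grades are recorded at each visit, and haemoglobin at its own time points, so either rule can be applied by program with no new data. Treatment and site vigilance do not change.

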**7.2.3 Reporting of adverse events:**

For each possible adverse event identified and graded as moderate, severe or life threatening, an adverse event report form will be completed (Appendix 15). An adverse event report form will not be completed for events classified as mild as these symptoms are common and difficult to distinguish from signs and symptoms due to malaria (however, mild AEs will still be included in the analysis). The following information will be recorded for all adverse experiences that are reported:

1. Description of event
2. Date of event onset
3. Date event reported
4. Maximum severity of the event
5. Maximum suspected relationship of the event to study medication
6. Is the event serious?
7. Initials of the person reporting the event
8. Was the event episodic or intermittent in nature?
9. Outcome
10. Date event resolved

Serious adverse events occurring in the trial shall be reported to the core facility by telecommunication within 24 hours. All information submitted by the surveillance sites will be collected at the Kampala core facility and reported to the Ugandan National Drug Authority and MoH.

### 7.3. Management of clinical treatment failures:

Patients who are classified as clinical failures (early or late treatment failure, Appendix 3) will be treated with quinine 10 mg/kg orally three times a day for 7 days. Any patient who develops evidence of severe malaria or danger signs during malaria follow-up, will be referred for appropriate treatment with parenteral quinine at the local facility or hospital. Any patient who responds clinically to treatment, but has a positive thick blood smear on day 28 (asymptomatic parasitaemia) will be treated with standard doses of oral quinine. Hemoglobin will be repeated on the day the patient is classified as a clinical treatment failure.

- 1. **Exclusion after enrolment and loss to follow-up:**

Patients will be excluded from the study after enrolment if any of the following occurs:

- 1. Use of antimalarial drugs outside of the study protocol.
  2. Development of concomitant febrile illness that may interfere with outcome classification.
  3. Withdrawal of informed consent.

Patients who fail to attend a follow-up visit and are unable to be located within 24 hours on Days 1-3 or within 48 hours on Days 4-28 will be considered lost to follow-up.

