**Severe disease or danger signs**

Urgent reading of thick blood smear

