**Negative**

Assess for DDx

Continue study Rx

Refer for care?

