**Positive blood smear**

**ETF**

Rx with quinine

Refer for care?

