### APPENDIX 3. OUTCOME CLASSIFICATION

### Clinical Outcome Classification System

| ACR (Adequate Clinical Response)   - Absence of parasitemia on Day 28, without previously meeting criteria for ETF or LTF - Temperature < 37.5C (Axillary) and no history of fever in last 24 hours on day 28 irrespective of the presence of parasitemia, without previously meeting any of the criteria of ETF or LTF |
| --- |
| ETF (Early Treatment Failure): Days 0, 1, 2, and 3  - Development of danger signs or severe malaria on Days 0-3 in the presence of parasitemia - Parasitemia on Day 2 higher than Day 0 count irrespective of temperature - Temperature > 37.5C (Axillary) on Day 3 in presence of parasitemia - Parasitemia on Day 3 > 25% Day 0 count |
| LTF (Late Treatment Failure): Days 4 To 28  - Development of danger signs or severe malaria on Days 4 to 28 in the presence of parasitemia, without previously meeting any of the criteria of ETF. - Temperature > 37.5C (Axillary) or history of fever in last 24 hours on Days 4 to 28 in the presence of parasitemia, without previously meeting any of the criteria of ETF. |

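### For danger signs with a negative smear, section 7.3 and Appendix 2 disagree on quinine, and Appendix 3 can score a quinine-treated patient as a success

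*Protocol*

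**What the plan says.** **Rescue rule.** Protocol section 7.3 first gives the treatment for patients classified as clinical failures, then adds: "Any patient who develops evidence of severe malaria or danger signs during malaria follow-up, will be referred for appropriate treatment with parenteral quinine". The sentence does not mention the smear.

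**Flow chart.** Appendix 2 starts from danger signs with "Urgent reading of thick blood smear". Management then splits. Under "Positive blood smear" the patient is an early treatment failure (ETF) or late treatment failure (LTF) and receives quinine. Under a negative smear the site assesses other diagnoses, is told "Continue study Rx", and finds referral posed as an open question.

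**Outcome definitions.** In the clinical classification of Appendix 3, the ETF criterion is "Development of danger signs or severe malaria on Days 0-3 in the presence of parasitemia" and the LTF criterion is "Development of danger signs or severe malaria on Days 4 to 28 in the presence of parasitemia". One route to ACR is "Absence of parasitemia on Day 28, without previously meeting criteria for ETF or LTF". The other is no fever on Day 28 and no fever history in the preceding 24 hours, whatever the smear, again without earlier ETF or LTF. Section 4.2.1 makes ACR the success category of the primary outcome.

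**Exclusion and CRF.** The list of exclusions after enrolment, which follows section 7.3, names "Use of antimalarial drugs outside of the study protocol". The outcome page of the CRF (Appendix 15) lists use of another antimalarial as an exclusion reason without that qualifier. It also offers a failure reason for a severe adverse event that forces a change of treatment on Days 0–2, which Appendix 3 does not contain.

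**The concern.** The rescue rule and the endpoint definition do not meet for one kind of patient: danger signs, no parasites on the smear. Two sites could each follow a page of the protocol correctly and give this patient different care. They could also record different outcomes. At a site that follows section 7.3, the patient receives a second antimalarial, is not a failure under Appendix 3, and can be scored a success on Day 28. At a site that follows Appendix 2 and gives no quinine, the same patient stays exposed to a late failure that would be counted.

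Two things are at stake: consistent care of a seriously ill patient, and a primary outcome in which rescue treatment given under the protocol might turn a later failure into a success. The planned failure counts are small, so the coding of single patients should not depend on which page a site has open.

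**Working it through.** **1. Trace the patient through the protocol.**

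- *Severity.* Section 5.2 and Appendix 13 define danger signs without reference to parasitaemia, so a smear-negative patient can have them.
- *Treatment.* Section 7.3 refers the patient for parenteral quinine. The negative branch of Appendix 2 continues study treatment and leaves referral open. Study drug is given on Days 0, 1 and 2 (section 6.3.2), so among follow-up days this direct clash is limited to Days 1–2. The connecting lines of the flow chart should be checked, but an instruction to continue study treatment has meaning only on dosing days.
- *Failure.* Both danger-sign criteria in Appendix 3 require parasitaemia, so the event itself is neither ETF nor LTF.
- *Follow-up.* Appendix 10 ends formal follow-up when a patient is classified as a failure. This patient is not, so follow-up can run to Day 28.
- *Success.* Both ACR routes ask only about Day 28 and earlier ETF or LTF. Neither asks about quinine.

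The gap on Days 1–2 is therefore both clinical and statistical. From Day 3 it is that section 7.3 gives quinine while Appendix 3 records no failure.

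**2. Check each possible safeguard.**

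- *Exclusion for antimalarials.* The protocol text covers drugs outside the protocol, but section 7.3 itself directs this quinine. The CRF tick box has no such limit. One document therefore supports both keeping and excluding the patient.
- *Exclusion for a concomitant febrile illness.* It catches some patients, but danger signs need not come with fever or another diagnosis.
- *CRF failure reason for a severe adverse event.* It covers Days 0–2 only and is absent from Appendix 3.
- *Repeated vomiting.* Sections 4.4 and 6.2 make inability to retain the dose on Day 1 or 2 a failure whatever the smear. This covers one presentation on two days.
- *Serious adverse event rule.* Appendix 10 classes the signs of severe malaria treated with parenteral quinine as serious adverse events but assigns no efficacy outcome.

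**3. Size.** The concern does not rest on a figure, and the documents give no frequency for this event.

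The sample sizes in section 8.1 reproduce. With two-sided α = 0.05, 80% power and continuity correction, 15% vs 5% gives 160 per group and 10% vs 2% gives 162. Dividing by 0.90 gives 178 and 180, stated as 180.

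- Expected failures in an alternative arm: 0.05 × 160 = 8 and 0.02 × 162 = 3.2.
- Weight of one patient: 1/160 or 1/162, about 0.6 percentage points.
- Miscounted failures = rescued smear-negative patients × their risk of a later failure. *Assume* 2–3 rescued patients in an arm, each at the planned risk of 2–15%. The range is 2 × 0.02 = 0.04 to 3 × 0.15 = 0.45 failures. That is 0.04/162 = 0.02 to 0.45/160 = 0.3 percentage points, against planned differences of 8 and 10 points.

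A harsher illustration moves 0.5%, 1% or 2% of the chloroquine plus sulfadoxine-pyrimethamine (CQ/SP) arm from failure to success, with the comparator unchanged. Power is computed without continuity correction at the stated n. The last column is the shift divided by the CQ/SP failure risk.

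| Design | Shift | Power | CQ/SP share rescued while smear-negative that this needs |
|---|---|---|---|
| 15% vs 5%, n = 160 | none | 85.0% | – |
| | 0.5% | 82.0% | 0.005/0.15 = 3.3% |
| | 1% | 78.7% | 0.01/0.15 = 6.7% |
| | 2% | 70.7% | 0.02/0.15 = 13.3% |
| 10% vs 2%, n = 162 | none | 86.2% | – |
| | 0.5% | 82.9% | 0.005/0.10 = 5% |
| | 1% | 79.2% | 0.01/0.10 = 10% |
| | 2% | 69.9% | 0.02/0.10 = 20% |

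Nothing in the protocol suggests rescue shares of this order, so these rows show sensitivity and are not a forecast.

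**The case against.** The best defence is that the protocol did not mean what section 7.3 says literally. The section is headed as management of treatment failures, and Appendix 10 speaks of patients who develop danger signs and require parenteral quinine, which makes quinine sound conditional. Appendix 2 does not forbid referral. On paper, many such patients would leave the success category through the CRF exclusion box, the febrile-illness exclusion, the CRF adverse-event failure reason or the vomiting rule.

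Part of this stands. The clash over study drug is confined to Days 1–2, referral is left open, and several routes away from ACR exist. But the sentence in section 7.3 covers any patient with danger signs, comes after a separate sentence on classified failures, and carries no smear condition. The routes away from ACR are incomplete and lead to different codes: excluded, failed or success.

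Three stronger readings are tempting and are not supported.

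- A reader might infer that an arm with faster parasite clearance gains, because its patients move from ETF to success. A smear-negative patient is not a danger-sign ETF with or without quinine, and fewer parasites on early days is a treatment effect. Section 4.2.2 lists parasite clearance as a comparison and states no expected difference.
- A reader might count every rescued patient as an error, so that 2–3 patients would shift an arm by 2/162 = 1.2 to 3/160 = 1.9 points. Only those who would later have failed are miscounted.
- A reader might conclude that all such patients must be failures. Some will have a non-malarial illness, so that coding is debatable. Censoring at the quinine date is no substitute, because section 8.2 compares dichotomous outcomes with chi-square or Fisher's exact tests.

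**Conclusion.** The point holds as an inconsistency with a limited effect on the primary endpoint. For danger signs with a negative smear, section 7.3 and Appendix 2 give different instructions on Days 1–2. Through Day 28, the Appendix 3 definitions allow a patient given quinine under the protocol to be scored ACR. The exclusion text and the CRF do not settle the code because they disagree with each other and with Appendix 3.

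The only distortion that the text supports is quinine suppressing a later LTF. Its size is unknown. It is about 0.02–0.3 percentage points in an arm if 2–3 patients are affected and they carry the planned failure risks. Both conditions are assumptions. Neither a bias in favour of one arm nor a material loss of power is shown. The reason to act is that one patient should receive one rule and one code at every site, and the change is cheap.

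**What to change.** Reconcile section 7.3, Appendix 2, Appendix 3 and the CRF so that every site follows one rule for danger signs with a negative smear. Which rule is the investigators' choice. Align the antimalarial exclusion in the protocol text with the CRF tick box, and either define the CRF adverse-event failure reason in Appendix 3 or remove it from the form.

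In Appendix 3 and section 4.2.1, state that a patient given study-directed quinine before Day 28 without meeting ETF or LTF is not automatically ACR. Prespecify one primary outcome code for these patients and apply it in all arms. Identify them from CRF items 60–70, which record additional medication with its indication, start date and study day. Quinine given at the referral facility must be entered there too. Tabulate them by arm and show the primary comparison with them coded the other way.

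The cost is wording in four places and one flag derived from data already collected. The small downside is that a few patients with a non-malarial illness may not count as successes. The recoded comparison shows whether that matters.
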